#### Exclusion criteria

3.5.2

Participants will be excluded if any of the following are present:

Known cases of Hypertension, Thyroid disorders, and Diabetes Mellitus.Those who require Hormone replacement therapy (HRT) during their menopausal period.PHQ-9 Depression scale Score greater than 5 at screening.Under medication for any psychological or psychiatric disorders & substance use in the past 30 days.Any active medical/ neurological conditions causing sleep disruption.No access to mobile phones and internet.Engagement in rotating shift work, night shifts, or occupations that involve irregular sleep–wake cycles, or any known lifestyle factors that disrupt normal sleep timing.Use of sleep-inducing medications, anti-depressants, anti-psychotics, or sedatives in the past 30 days.Body Mass Index (BMI) > 35.

BMI will be measured using a calibrated digital weighing scale and stadiometer at screening. PHQ-9 will be administered in paper format and scored immediately during the screening visit to determine eligibility.

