### Participant timeline

4.3

Enrolled participants follow a sequence of screening, baseline intervention and follow up. During the initial screening (Week 0), the medical officer document demographic details, perimenopausal status (STRAW staging), and chronic insomnia symptoms which is occurring at least three nights per week for the past 3 months. Screening evaluations will include the Insomnia Severity Index (ISI) to determine eligibility, PHQ-9 to rule out depressive symptoms (≤5), review of recent medication use, and assessment of BMI (≤35). Baseline medical history, lifestyle factors (sleep schedule regularity, shift-work exclusion), and technology readiness (phone/internet access) will be verified. *Prakriti* (constitutional profile) assessment and documentation of baseline *Dosa dushti lakshaṇa* (etiopathogenesis with clinical presentation) related to *Nidranasa* (disturbance or loss of sleep) will be completed for descriptive and exploratory analysis. Written informed consent will be obtained at this stage. Following the screening visit, participants will attend a baseline assessment session, during which ISI, PSQI, sleep diary orientation, safety checks, completing the clinical evaluation. Screening and baseline visit may occur on the same day if eligibility is confirmed and consent is obtained. Following which a baseline evaluation is done and, participants are randomized into 1:1 groups. Participants in the add- on arm will receive *Siro-pichu* (7 days) and *Padabhyanga* twice daily (14 days) with demonstration, training and home based adherence monitoring, while both groups receive sleep hygiene education and eight twice-weekly sessions of CBT-I delivered by certified psychologists. Sessions will follow a structured CBT-I manual that includes sleep restriction, stimulus control, cognitive restructuring, relaxation training, and relapse-prevention modules. Adherence will be monitored through attendance logs, sleep diaries, DSTED entries, and telephonic check-ins. Upon completion of the intervention period (at Week 4), participants will attend an assessment post-intervention visit to repeat ISI, PSQI, and other outcome measures.

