#### Data collection procedures

4.8.1

Study data will be captured via standardized paper-based case record forms (CRFs) and validated outcome instruments. Trained research staff, independent of intervention delivery, will oversee data collection at the Outpatient Department (OPD) during screening and baseline. Subsequent intervention (Weeks 2, 4) and follow-up (Weeks 6–16) assessments will occur in person or via telehealth. Outcome instruments (ISI, PSQI, SDS, DSTED) are self-administered by participants under supervision of trained research staff independent of intervention delivery. Research staff may clarify instructions but will not influence responses (Table 1).

**Table 1 tab1:** Data collection methods.

Trial instrument	Purpose	Frequency of measurement	Timepoints of assessment
Insomnia Severity Index	To determine the primary outcome: severity of insomnia symptoms over the preceding two weeks	Every 2 weeks	Baseline (Week 0), Week 2, Week 4 (end of intervention), Week 6, Week 8, Week 12, Week 14, Week 16 (end of follow-up)
Pittsburgh Sleep Quality Index	To evaluate the overall sleep quality and its domains, including latency, duration, efficiency over the past month	Monthly	Baseline (Week 0), Post- treatment (Week 4), Follow-up Months 1, 2, and 3
ADR Monitoring Checklist	To identify and document any adverse events or reactions related to the integrative intervention	Ongoing monitoring at each contact point	Weekly during intervention (Weeks 0– 4), and monthly during follow-up (Months 1–3)
Severity of dependency Scale	To detect any signs of behavioral or psychological dependency on *Śiro-pichu* and *Pādābhyanga* therapies	Twice during the study	Post-intervention (Week 4), End of follow-up (week 16)
Daily Sleep and Treatment Engagement Diary	To assess adherence and consistency in following the prescribed intervention protocol	At the end of intervention and follow up	Week 4 of intervention, Week 16 of follow up

Official Malayalam versions of ISI and PSQI were obtained from ePROVIDE–MAPI Research Trust (COA request submitted 08-Aug-2025; approval date: 01 September 2025). Instruments will be administered in accordance with licensing terms. Table 1 shows the data collection methods in detail.

Sleep diaries will record total sleep time (TST). For descriptive summaries, TST will be categorized as optimal (7–9 h), short (<6 h), or long (>9 h). Classification is for characterization only and will not determine treatment response.

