#### Exploratory secondary outcome analysis

4.9.2

Follow-up ISI and PSQI scores beyond Week 4 will be summarized descriptively. Data will be presented as mean ± SD or median (IQR), and graphical trends over time will illustrate within-group patterns. No formal repeated measures ANOVA or confirmatory longitudinal modeling is planned. These analyses are exploratory and not adjusted for multiple comparisons. Sleep-duration categories (<6 h, 7–9 h, >9 h) will be used for descriptive summaries and exploratory subgroup analysis. No confirmatory inference will be based solely on duration categories. Adverse events will be summarized by frequency and proportion in each group. Between-group comparisons will be explored using Chi-square or Fisher’s exact tests. Severity of Dependence Scale (SDS) scores and adherence percentages will be summarized descriptively and compared between groups using appropriate parametric or non-parametric tests. Findings will be interpreted as exploratory.

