### Subgroup analyses

4.11

Exploratory subgroup analyses will be conducted to examine whether treatment effects vary across key demographic and clinical characteristics. Subgroups will include age categories (45–50 vs. 51–55 years), BMI classifications (normal vs. overweight), and baseline insomnia severity (sub-threshold vs. moderate insomnia based on ISI scores). In addition, Ayurvedic baseline assessments—including *Prakriti* (individual body constitution) profiling and documentation of *Dosha dushti lakshana (symptoms associated)* associated with *Nidranasa*—will be incorporated to explore potential correlations between *Dosha* predominance and insomnia severity. These analyses are exploratory in nature and intended to generate hypotheses for future confirmatory studies. All statistical analyses will be performed using R version (4.1.5).

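### The sleep-duration bands leave 6 to under 7 h unclassified, and the duration subgroup probably rests on diary data recorded after randomization

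*Protocol article*

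**What the plan says.** Section 4.8.1 (Data collection procedures) names the source, "Sleep diaries will record total sleep time (TST"), and the bands: "TST will be categorized as optimal (7–9 h), short (<6 h), or long (>9 h"). It then limits their use: "Classification is for characterization only and will not determine treatment response".

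Section 4.9.2 (Exploratory secondary outcome analysis) repeats the bands with a wider use: "Sleep-duration categories (<6 h, 7–9 h, >9 h) will be used for descriptive summaries and exploratory subgroup analysis". It adds that no confirmatory inference will rest on these categories alone. The subgroup list in section 4.11 does not name sleep duration.

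On timing, section 4.3 (Participant timeline) says that "participants will attend a baseline assessment session, during which ISI, PSQI, sleep diary orientation, safety checks" take place, with randomization afterwards, and that "Screening and baseline visit may occur on the same day if eligibility is confirmed and consent is obtained". Section 3.6.3.1 puts instruction on the sleep diary in CBT-I Session 1. Table 1 lists the Daily Sleep and Treatment Engagement Diary at Weeks 4 and 16 and the PSQI from Week 0.

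**The concern.** A classification used in tables and in a subgroup analysis has to place every participant. This one has a one-hour hole, in a range where women with insomnia could plausibly fall. If the hole is found only at analysis, someone must decide after seeing data whether those women are short sleepers, optimal sleepers or a new group.

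The subgroup use raises a second problem. Comparing arms within bands keeps the protection of randomization only if the banding variable was fixed before treatment. If the add-on lengthens sleep for some women, the 7–9 h band in that arm includes women whom the add-on moved there, while the same band in the control arm holds women who reached it on CBT-I alone. The two sets are no longer comparable, and a difference in ISI change between them could reflect selection. An exploratory label does not remove that bias, and this trial is meant to inform the design of the next one.

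**Working it through.** **1. Do the bands cover every value?** Applying the stated rule:

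| Total sleep time | Band |
|---|---|
| 5.9 h | short |
| 6.0 h | none |
| 6.5 h | none |
| 6.99 h | none |
| 7.0 h | optimal |
| 9.0 h | optimal |
| 9.1 h | long |

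The gap is 6 h ≤ TST < 7 h, where TST is total sleep time. The same cut-points stand in sections 4.8.1 and 4.9.2. They match the educational message in section 3.6.3.2, which calls 7–9 h beneficial and under 6 h insufficient. That works as advice, but it does not partition a sample.

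**2. How many women could fall in the gap?** The protocol gives no figure to reproduce. From the documents: N = 62 (section 4.5). Assumed: one TST value per woman, normally distributed with mean μ and SD σ. Then

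P(6 ≤ TST < 7) = Φ((7 − μ)/σ) − Φ((6 − μ)/σ), and expected number = 62 × P.

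Worked case, μ = 6, σ = 1: Φ(1) − Φ(0) = 0.841 − 0.500 = 0.341; 62 × 0.341 = 21.2.

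| μ (h) | σ = 0.8 | σ = 1.0 | σ = 1.3 |
|---|---|---|---|
| 5.0 | 0.099 (6.2) | 0.136 (8.4) | 0.159 (9.9) |
| 5.5 | 0.236 (14.6) | 0.242 (15.0) | 0.226 (14.0) |
| 6.0 | 0.394 (24.4) | 0.341 (21.2) | 0.279 (17.3) |
| 6.5 | 0.468 (29.0) | 0.383 (23.7) | 0.299 (18.6) |
| 7.0 | 0.394 (24.4) | 0.341 (21.2) | 0.279 (17.3) |

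Each cell gives the probability, with the expected number of 62 women in brackets. The range is 10% to 47%, about 6 to 29 women.

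**3. What may the bands be used for?** Section 4.8.1 confines them to characterization. Section 4.9.2 adds subgroup analysis. Section 4.11, which lists the subgroups, leaves duration out. The three places do not agree.

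**4. When is diary TST recorded?** Before randomization the protocol describes only orientation to the diary, at a session that may fall on the screening day. Instruction in its use belongs to CBT-I Session 1. No run-in is described, and no diary window is named for the bands. Recording after randomization is therefore the likely reading, though it is not stated.

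**5. Could treatment move TST differently by arm?** Both arms receive the same CBT-I, including sleep restriction (section 3.6.3), so that component alone gives no difference between arms. Section 8.2, however, lists better sleep duration among the possible benefits of the combined intervention. The protocol thus allows that the add-on changes the variable used to form the subgroup.

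**The case against.** The strongest reply is that little depends on these bands. TST is neither a primary nor a listed secondary outcome, the subgroup use is one phrase in section 4.9.2, and confirmatory inference from the bands alone is ruled out. This limits the weight of the point. It does not close the gap or reconcile the stated uses.

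Three stronger readings are tempting and are not supported.

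- A reader might take it as fact that diary TST is measured after treatment starts. No section says which diary days define the bands. The absence of a baseline entry for the engagement diary in Table 1 does not settle it, because that row concerns adherence and section 4.3 lists sleep diaries and that diary separately. A full analysis plan could name a window.
- A reader might infer that sleep restriction in itself biases the subgroup comparison. Both arms receive it. Bias needs a differential effect of the add-on on TST, which is plausible but not established, so the estimates could be biased rather than must be.
- A reader might extend the gap to BMI, because section 4.11 names only "BMI classifications (normal vs. overweight") while section 3.5.2 excludes only "Body Mass Index (BMI) > 35". No cut-offs are given, and overweight may mean everything above normal. The documents do not show that obese women are left out.

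**Conclusion.** The gap is certain: it follows from the stated cut-points and occurs in both sections. The share of women affected is unknown, and the 10% to 47% range rests wholly on the assumed normal distribution. The conflict between characterization only and subgroup use is also plain on the page.

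That the duration subgroup would condition on a post-randomization variable is a probable inference, and any bias depends on the add-on altering sleep time. The consequences are confined to the duration summaries and the exploratory duration subgroup. The primary ISI comparison, the sample size and the listed secondary outcomes are untouched. The point should be corrected before analysis, but it does not threaten the trial's main result.

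**What to change.** In sections 4.8.1 and 4.9.2, replace the bands with an exhaustive set: under 6 h, 6 to under 7 h, 7–9 h and over 9 h. The educational message in section 3.6.3.2 can stay as it is.

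Report diary TST by arm as a descriptive outcome only, and remove the subgroup use of diary TST from section 4.9.2 so that it agrees with section 4.8.1. If a duration subgroup is wanted, define it on the sleep-duration item of the baseline PSQI, which Table 1 already schedules at Week 0 with a recall period of the past month, and add it to the list in section 4.11.

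The cost is a few sentences, with no new data and no change to the sample size. The changes should be made before the data are analysed, so that the missing band is not assigned after the fact.

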#### Quality control and verification

4.8.2

Completed CRFs will be reviewed on the same day by supervising research staff. Within 24 h, the Principal Investigator or designated Co-Investigator will verify completeness, internal consistency, and protocol adherence.

ADR/AE checklists and DSTED entries will be reviewed at each contact. Data verification will occur before entry into the electronic database.

#### Documentation and confidentiality

4.8.3

All study documentation will be maintained in paper format. Prior to enrolment, potential participants will receive the PIS and ICF in English and Malayalam. Written informed consent will be obtained before initiation of any study procedures. Each participant will be assigned a unique study ID code used on all CRFs and instruments. Personal identifiers will be recorded only on consent forms and screening logs and stored separately from analytical datasets. Paper documents will be stored in locked cabinets within the Department of Prasuti Tantra and Striroga. Access will be restricted to authorized study investigators.

#### Retention

4.8.4

Participation in this study is entirely voluntary. Participants may withdraw at any time without penalty or loss of entitled care and this will be documented in study records. Participants who withdraw will not undergo any additional data collection or follow-up assessments. Data collected prior to withdrawal will be retained for analysis unless the participant explicitly requests removal, subject to regulatory and ethical guidelines. Efforts will be undertaken, where appropriate and ethically permissible, to minimize unnecessary dropouts while respecting participant autonomy. All study records will be retained for a minimum of 5 years following study completion in accordance with institutional policy and Indian Council of Medical Research (ICMR) guidelines.

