### Withdrawal criteria

3.8

Participants may be withdrawn from the study under the following circumstances:

Occurrence of a serious adverse event requiring urgent medical intervention.Initiation of pharmacological treatment for insomnia during the study period.Emergence of a psychiatric condition requiring immediate clinical management.Voluntary withdrawal of consent.

Symptom fluctuation or worsening insomnia severity alone will not constitute automatic withdrawal. Participants experiencing worsening symptoms will undergo clinical evaluation and supportive management. Non-compliance with the intervention schedule will be documented but will not automatically result in withdrawal. All randomized participants will be included in the intention-to-treat analysis wherever feasible.

Withdrawal decisions due to safety concerns will be made by the Principal Investigator in consultation with the Co-Investigator and documented in the CRF.

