### Handling missing data & population analysis

4.10

Primary analysis: Intention-to-treat (ITT).Missing data management: Multiple imputation will be used if missing exceeds 10% and a per-protocol analysis will be done alongside ITT analysis to assess robustness.

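### Withdrawal for starting an insomnia drug ends all outcome collection, so Week 4 and follow-up ISI can be lost for outcome-related reasons that the intention-to-treat and imputation rules do not repair

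*Protocol article*

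**What the plan says.** Four statements in the protocol article bear on this point.

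- **Section 3.8, Withdrawal criteria.** The list opens with "Participants may be withdrawn from the study under the following circumstances" and includes "Initiation of pharmacological treatment for insomnia during the study period". A serious adverse event needing urgent care, an emergent psychiatric condition and withdrawal of consent stand in the same list, with no distinction in what happens next. The section adds "Symptom fluctuation or worsening insomnia severity alone will not constitute automatic withdrawal", and then "All randomized participants will be included in the intention-to-treat analysis wherever feasible".
- **Section 4.8.4, Retention.** "Participants who withdraw will not undergo any additional data collection or follow-up assessments". The next sentence says "Data collected prior to withdrawal will be retained for analysis unless the participant explicitly requests removal".
- **Section 4.10, Handling missing data & population analysis.** Intention-to-treat is the primary analysis, and "Multiple imputation will be used if missing exceeds 10% and a per-protocol analysis will be done alongside ITT analysis to assess robustness".
- **Section 4.1.** The primary outcome is the change in ISI from baseline to Week 4. Section 4.2 adds ISI and PSQI during follow-up to Week 16.

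**The concern.** Starting a sleep drug during an insomnia trial is a direct sign that the assigned treatment has not been enough. If that event leads to withdrawal from the study, and withdrawal ends all assessment, then whether a score exists depends on how the woman was doing. Such missingness cannot be assumed ignorable.

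It may also differ by arm. Section 1.2 gives lower reliance on medication as one aim of the add-on, and participants know their allocation. The event that stops data collection is thus one that the add-on is meant to make rarer.

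At stake is the between-arm ISI estimate. The trial is exploratory, but the estimate is its main product and is meant to guide the design of later trials. A score that was never collected cannot be recovered at the analysis stage.

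**Working it through.** **1. The plan's own figures.** Section 4.5 gives a difference of 4 points, SD 4.3, two-sided alpha 0.05, 90% power and 15% attrition.

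- n per group = 2 × 4.3² × (1.960 + 1.282)² / 4² = 24.3, which rounds up to 25.
- With the t distribution, power is 0.897 at 25 and 0.908 at 26, so 26.
- 26 / 0.85 = 30.6, so 31 per arm and 62 in total.

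The stated 26 and 31 reproduce. The point below does not affect the sample size.

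**2. The rules followed for one woman.**

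- *Drug started in Week 3, and she is withdrawn (3.8).* Collection stops (4.8.4). Baseline and Week 2 ISI are kept, but there is no Week 4 ISI.
- *Drug started in Week 7, and she is withdrawn.* The primary outcome exists, but ISI and PSQI from Week 8 onward are lost.
- *Insomnia worsens, no drug started.* Under 3.8 this alone is not automatic withdrawal. Under 3.10.3 significant worsening leads to a pause and a referral. She reaches the first two cases only if the referral results in drug treatment.

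**3. When imputation applies.** I read the 10% as the share of the 62 Week 4 ISI scores that are missing; the article does not say.

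- 10% × 62 = 6.2.
- 6 missing: 6/62 = 9.7%, so no imputation is triggered and no other method is given. A comparison of change scores then simply omits these women.
- 7 missing: 7/62 = 11.3%, so imputation is triggered.
- Planned attrition: 15% × 62 = 9.3, so imputation is triggered if attrition is as planned and falls before Week 4.

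**4. Size of the shift.** In an arm where a share f of women is lost, and these would have scored D points above those who remain, the mean of the remaining women is f × D below the mean of all women. Taking benefit as control minus add-on:

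shift in apparent benefit = −D × (f_control − f_add-on)

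The documents give neither f nor D. With 31 per arm, and D from 2 to 8 as an assumption:

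| Withdrawn, control vs add-on | f difference | D = 2 | D = 4 | D = 6 | D = 8 |
|---|---|---|---|---|---|
| 3 vs 0 | 3/31 = 0.097 | −0.19 | −0.39 | −0.58 | −0.77 |
| 6 vs 0 | 6/31 = 0.194 | −0.39 | −0.77 | −1.16 | −1.55 |
| 3 vs 3 | 0 | 0 | 0 | 0 | 0 |

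Against the planned 4 points, 1.55 is 39%. If the extra losses were in the add-on arm, the sign would reverse.

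**5. Is D = 8 too large?** I simulated Week 4 scores as normal with means 10.9 and 6.9 and SD 4.3, and removed exactly the worst control scorers. Losing the worst 3 lowers the control mean from 10.9 to 10.12, a shift of 0.78. Losing the worst 6 lowers it to 9.49, a shift of 1.41. So D = 8 is about the ceiling for 3 losses and slightly beyond it for 6.

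**6. Does 4.10 repair this?** Above the trigger, imputation from scores taken before withdrawal recovers the part that baseline and Week 2 ISI predict. It does not recover the deterioration that led to the drug start unless the reason for loss is modelled. A per-protocol analysis removes further women and leaves the assumption about the missing scores untested.

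**The case against.** Much can be said for the plan.

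- **Worsening is not a withdrawal reason.** A reader might infer that women are withdrawn because they get worse. Section 3.8 says otherwise, and adds: "Participants experiencing worsening symptoms will undergo clinical evaluation and supportive management". Non-compliance does not lead to automatic withdrawal either. This stands: the route from worsening to lost data is indirect.
- **Withdrawal is discretionary.** The word in 3.8 is may, so not every woman who starts a drug is lost. This stands too, but a discretion without stated criteria does not make the missingness ignorable.
- **Section 4.8.4 is written around voluntary withdrawal.** Ending collection after consent is withdrawn is normal. However, 3.8 puts drug start beside withdrawal of consent as one kind of withdrawal, and 4.8.4 makes no exception. Clarification is the least that is needed.
- **Earlier data are kept, and imputation is the expected case at 15% attrition.** Correct. Complete omission from the Week 4 comparison arises only at 6 or fewer missing.
- **The imputation model may be set out in the full analysis plan.** Agreed. Its absence from the article is not part of this point.
- **The size is assumed.** Six drug-start withdrawals before Week 4 would use 6 of the 9.3 losses allowed for all causes, in women with ISI 8–21 and no recent sedative use. If a drug brought scores back to the level of the women who remain, D would be near zero. With SD 4.3 and 26 per arm the 95% interval has a half-width of about 2.4 points, so every shift in the table lies inside it. That lowers the urgency. It does not remove a systematic error that the interval does not show.

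**Conclusion.** The concern holds in a limited form. Sections 3.8 and 4.8.4, followed as written, allow a drug start to end outcome collection. The resulting gaps in Week 4 and follow-up ISI and PSQI are related to outcome. The intention-to-treat analysis in 3.8 and 4.10 therefore cannot be fully delivered, and neither the 10% trigger nor the per-protocol analysis makes up for that.

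A reader might go further and say that the primary analysis is not intention-to-treat at all. The documents do not support this: all randomized women belong to the analysis set where feasible, data from before withdrawal are kept, and imputation is planned above 10%. The set is right, but its data would be incomplete by design.

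The size depends on assumed withdrawal counts and an assumed D of 2 to 8 points. It is about 0.2 to 0.8 points for 3 against 0 and about 0.4 to 1.55 for 6 against 0, with the top of the second range beyond what losing the six worst scorers would produce. It is zero for equal losses with equal D. These are the shifts when lost scores are simply omitted; imputation from earlier scores would reduce them in part. More losses in the control arm would shrink the apparent benefit, and more in the add-on arm would inflate it.

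**What to change.** Reconcile 3.8, 4.8.4 and 4.10, leaving every clinical rule as it is.

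1. In 3.8 and 4.8.4, separate stopping study treatment from withdrawing consent to further contact. State that stopping study treatment or starting an insomnia drug does not end outcome collection. Only women who withdraw consent to further contact stop.
2. Have all other women complete ISI and PSQI at Week 4 and at later scheduled visits, in person or by the telehealth route already in 4.8.1. Include these observed scores in the intention-to-treat analysis.
3. In 4.10, delete the 10% trigger, so that any missing Week 4 ISI is imputed using baseline and Week 2 ISI.
4. Keep the per-protocol analysis if wanted, but do not present it as the robustness check for missing data.

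The cost is a protocol amendment and a few extra questionnaires. There is one small downside: the estimate will include the effect of any drug started. The change needs to be made while the women can still be followed up.
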